## Abstract

**Introduction:**

Community-acquired pneumonia has high mortality and is associated with significant healthcare costs. In older adults with community-acquired pneumonia neutrophil dysfunction has been identified and is associated with poor outcomes for patients. Immunometabolism is a rapidly developing field which links immune cell function to metabolism. This study aims to explore neutrophil metabolism in community-acquired pneumonia.

**Methods and analysis:**

Pneumonia Metabolism in Ageing study is a prospective observational study recruiting older adults hospitalised with community-acquired pneumonia to examine neutrophil function and metabolic status. Controls will be older adults with no acute illness. The primary endpoint is neutrophil chemotaxis.

**Ethics and dissemination:**

The study has ethical approval from the Research Ethics Committee Wales, reference 19/WA/0299. This study involves participants who may lack the capacity to consent to research involvement, in this situation, personal or professional assent will be sought. The results from this study will be submitted for publication in peer-reviewed journals and disseminated at local and international conferences.

WHAT IS ALREADY KNOWN ON THIS TOPICNeutrophils from older adults with community-acquired pneumonia demonstrate altered effector functions compared with younger adults. However, the mechanism underlying the broad dysfunction seen remains unclear.WHAT THIS STUDY ADDSThis study investigates neutrophil metabolism, a novel aspect of neutrophil biology in pneumonia and sepsis.HOW THIS STUDY MIGHT AFFECT RESEARCH, PRACTICE OR POLICYThis study has the potential to lead to a new treatment paradigm in community-acquired pneumonia; targeting the host response alongside antimicrobial therapies.

## Introduction

Community-acquired pneumonia (CAP) is a leading cause of hospitalisation and has high mortality in older adults.^1^ Mortality is greatest in those with sepsis due to CAP (CAP+S), with survivors experiencing increased mortality for a decade following discharge from hospital.^2^ The long-term burden of CAP includes cognitive dysfunction, reduced mobility and increased care needs. Readmission following hospitalisation for CAP is common, occurring in 11% of older adults.^3^

CAP occurs most commonly in adults aged over 65 years, and older adults are more likely to experience severe CAP and CAP+S.^4^ As the global population is ageing the prevalence of CAP is likely to rise.^5^

Between 22% and 42% of all CAP episodes require hospitalisation,^6^ and this places a significant burden on health services. In 2019, hospital treatment for CAP cost the National Health Service £731 million, with costs significantly higher for the treatment of older adults.^7^

There have been no significant advances in the management of CAP since the advent of antibiotic therapy.

Recovery from CAP requires a functional and coordinated immune response. In CAP, neutrophils are the predominant responding immune cell to infection and the resulting tissue damage. Neutrophils migrate to sites of inflammation and clear infection through bactericidal effector functions including phagocytosis and the generation of neutrophil extracellular traps and reactive oxygen species (RoS).^8^ These functions can be encompassed by cellular phenotype; the manifestation of cellular processes at gene and protein levels which result in changes in a cell’s function, morphology and surface markers.^9^

In young adults, CAP is associated with a rapid upregulation of effector functions until the infection is resolved.^10 11^ However, even in health neutrophil functions in older adults appear depressed,^12^ this is particularly true in frail older adults^13^ and data suggest that CAP exacerbates this, with further reductions in neutrophil functions leading to a state of immunoparesis which has been demonstrated for up to 6 weeks following CAP.^12 14–16^ Differences in neutrophil cellular phenotype have been identified in sepsis^17^ and disease states such as chronic obstructive pulmonary disease,^18^ however, there is no literature examining changes in surface marker expression combined with functional assessment in CAP.

This broad impact on effector function suggests that a central cellular mechanism is involved, such as metabolism. Immunometabolism is defined as the role of cellular metabolism in the regulation of immune function^19^ and there is increasing interest in exploring if therapeutically targeting immunometabolism may optimise immune responses. For example, inhibiting glycolysis in myeloid cells using murine models is associated with an improved recovery from sepsis.^20^

Neutrophil metabolism is poorly understood, especially in disease states but neutrophils appear to rely on glycolysis for energy generation.^21^ The effector functions required for a coordinated and effective response to infection are highly energy-demanding processes. Modification of glycolysis in neutrophils may offer a novel therapeutic strategy for CAP. Potential targets include glucose transporters, key enzymes required for glycolysis (hexokinase, phosphofructokinase, pyruvate kinase and lactate dehydrogenase) and lactate transporters/receptors. Evidence to date confirms alterations in these key enzymes during sepsis.^22^

This manuscript describes a protocol for the assessment of neutrophil function, phenotype and immunometabolism in older adults with CAP, compared with an age, frailty and morbidity-matched cohort in the Pneumonia Metabolism in Ageing (PUMA) study.

## Study aims

### Research hypothesis and aims

We hypothesise that depressed neutrophil function seen in older adults with CAP is due to alterations in neutrophil immunometabolism, and that this alteration is modifiable in vitro by modulating glycolysis.

This study aims to functionally phenotype neutrophils from participants with CAP alongside age and frailty-matched cohort while characterising the metabolism of these cells. Figure 1 provides an overview of the study design and outcomes collected. Primary and secondary aims are outlined in table 1.

**Figure 1 F1:**
[figure not shown]
Schematic overview of study design and outcomes. (A) Older adults with and without community-acquired pneumonia (CAP) will be recruited, (B) we will collect a detailed medical history, record complications and outcomes of CAP, participants will donate whole blood used to isolate neutrophils. Isolated neutrophils will be functionally assessed (oxidative burst and migration), phenotype as assessed by cell surface markers and metabolic status will be measured. (C) Changes seen in function and metabolism will be assessed at RNA and protein levels. For CAP participants, further visits will be repeated at days 3–5 and day 42 following admission. Created with BioRender.com

**Table 1 T1:** Primary and secondary aims of the PUMA study

Primary aims:	Sequentially assess community-acquired pneumonia-related change in neutrophil phenotype Characterise neutrophil metabolism in cases and controls
Secondary aims:	Migration Oxidative burst Phenotype as defined by cell surface markers Transcriptomics Determine if neutrophil function can be prevented or restored by modulating neutrophil metabolism using targets involved in glycolysis

PUMA, Pneumonia Metabolism in Ageing.

## Methods

### Study design

PUMA is an observational cohort study recruiting adult participants with CAP as defined by the British Thoracic Society.^23^ This includes symptoms and signs consistent with an acute lower respiratory tract infection associated with radiographic shadowing for which there is no other explanation. Signs and symptoms include three or more of the following: cough, sputum production, breathlessness, pleuritic chest pain, haemoptysis, fever, headache and signs consistent with pneumonia on chest auscultation. Participants with and without sepsis will be recruited. Sepsis is defined as a quick Sequential Organ Failure Assessment score score ≥2.^24^

The control cohort will be matched as much as possible for age and frailty with no recent acute illness. Matching for frailty will be achieved using clinical frailty scale. Participants will be recruited between March 2020 and November 2024; however, there have been significant periods of disruption relating to the pandemic and other factors. Recruitment is ongoing.

Full inclusion and exclusion criteria for each cohort are in table 2. We have chosen to exclude patients with common conditions or medications known to significantly impact neutrophil function and or metabolism such as chronic obstructive pulmonary disease and haematological malignancy.^25 26^

**Table 2 T2:** Inclusion and exclusion criteria

Inclusion criteria	Exclusion criteria
CAP cohort	
Community-acquired pneumonia±sepsis admitted to hospital Age ≥65 years	Asthma Chronic obstructive pulmonary disease Metastatic malignancy Haematological malignancy Participants already enrolled in a study of novel/unlicensed treatment Immunosuppressive treatment in the preceding 12 weeks Known immunodeficiency syndrome Treatment withdrawal imminent Current infection with COVID-19
Control cohort	
Age ≥65 years	As above plus: Acute illness in preceding 12 weeks Unable to give informed consent to enrolment

CAP, community-acquired pneumonia.

The study will be conducted in a single site, at the Queen Elizabeth Hospital, Birmingham, UK (QEHB). The QEHB is a 1200-bed tertiary and acute hospital in an urban area.

### Sampling and sample size calculation

CAP cases will be recruited from inpatient wards at QEHB and are expected to remain admitted for ≥24 hours. Controls will be recruited from a range of outpatient clinics at QEHB to enable matching of age, frailty and comorbidity where possible.

The primary outcome measure for sample size calculation is based on a reduction in chemotaxis in patients with CAP compared with age-matched controls. Pilot data indicate a 62% reduction in chemotaxis in CAP cases with SD 0.079 for CAP and 0.135 for controls. To detect a difference in chemotaxis with p<0.005 and 95% power, we will need to recruit eight CAP and eight controls. In the completed SNOOPI study, a 30-day mortality was 16%, and study withdrawal was 6%.^11^ We estimate we need to recruit two CAP participants to account for drop-outs. Total sample size: 10 CAP and 8 controls. This limited sample size is not anticipated to inform relationships between clinical outcomes and neutrophil function but is powered to detect a biological endpoint (difference in neutrophil chemotaxis between CAP and controls).

### Study visit procedure

#### Participant identification, consent and follow-up

Where possible CAP participants will be recruited within 36 hours of hospital admission, then follow-up visits between day three and five (if remaining an inpatient) and then 6–8 weeks following admission, where possible the 6–8 weeks visit will be timed to coincide with follow-up chest radiograph when requested by the clinical team. Drop-outs to follow-up are expected due to death, discharge prior to days 3–5, withdrawal and unwillingness to return to hospital for 6–8 weeks visit. Study procedures are shown in figure 2. CAP frequently causes delirium, and dementia is a common comorbidity of older adults with CAP, therefore, CAP participants who lack the ability to consent to enrolment are not excluded. In the case of impaired capacity to consent to study enrolment a personal consultee opinion will be sought in the first instance, if no personal consultee is available an independent professional consultee’s opinion will be sought. Retrospective consent will be sought in these cases.

**Figure 2 F2:**
[figure not shown]
Study procedures for CAP participants. CAP participants will be recruited for baseline visit within 24 hours of admission, at this visit research blood samples will be taken alongside clinical bloods and demographic data collected. If remaining an in-patient at 3–5 days a further research blood sample will be collected. A visit at 6–8 weeks following admission will be arranged to coincide with follow-up imaging if requested by clinical team. Created with BioRender.com. CAP, community-acquired pneumonia.

Control participants will be recruited at a single time point only.

#### Data collection

At each study visit participants will undergo a detailed clinical history to ascertain factors which may influence neutrophil function, and outcome of CAP, as described in figure 3. We will also record information related to the hospital admission such as treatment strategies that may influence outcomes. Traditionally studies of CAP have considered binary outcomes such as survived/died, however, our public and patient involvement and engagement work demonstrated that a more nuanced approach was preferred. Therefore, we will collect information on postdischarge mobility, care needs and readmissions to hospital. Due to the limited size of the planned study, the comparisons using this data are intended to be exploratory and ensure the CAP and control cohorts are well matched.

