### Statistical analysis

Data will be analysed using SPSS for Windows V.26.0, GraphPad Prism V.9.0 or R V.4.2 or later. For continuously distributed data, differences between groups will be tested using independent sample t-tests with transformations of variables to normality if appropriate or non-parametric equivalents. χ^2^ tests (or Fisher’s exact tests) will be used for categorical variables. Any comparisons of clinical parameters such as impact of CAP severity will be considered exploratory.

The results of this study will be submitted to peer-reviewed journals for publication and will be presented at local and national conferences. We will adhere to Enhancing the QUAlity and Transparency Of health Research (EQUATOR) guidelines for observational studies and follow International Committee of Medical Journal Editors (ICMJE) best practice in generation of the study manuscript. No participants will be identified in publications that result from this study.

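### Comparing 10 CAP participants with 8 controls can describe how well the cohorts match but cannot ensure it, and a non-significant difference must not be read as matched

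*Protocol article*

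**What the plan says.** Matching is planned at recruitment, without a stated tolerance. Under Study design: "The control cohort will be matched as much as possible for age and frailty with no recent acute illness", and "Matching for frailty will be achieved using clinical frailty scale". Under Sampling and sample size calculation, controls come from several outpatient clinics "to enable matching of age, frailty and comorbidity where possible". The planned size is stated there too: "Total sample size: 10 CAP and 8 controls".

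Data collection then gives the clinical data a second role: "the comparisons using this data are intended to be exploratory and ensure the CAP and control cohorts are well matched". It names no balance measure, no threshold and no action if the cohorts differ.

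The between-group methods are in Statistical analysis. For continuous data, "differences between groups will be tested using independent sample t-tests with transformations of variables to normality if appropriate or non-parametric equivalents"; for categorical data, χ² "tests (or Fisher’s exact tests) will be used for categorical variables". No adjusted or matched-pair analysis is described.

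**The concern.** Two things are being asked of the comparison that it cannot deliver. It cannot ensure matching, because that depends on whom the study recruits. And if it takes the form of the stated tests, a non-significant result in 18 people mainly reflects the small sample.

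Balance matters here on the protocol's own account. The Introduction says that neutrophil function is reduced in older adults even in health, and more so in the frail. Imbalance is also foreseeable. CAP participants who lack capacity may enrol, and dementia is named as a common comorbidity among them, whereas controls who cannot consent are excluded (Table 2) and are outpatients. If the CAP cohort turns out frailer, part of its apparent loss of function could be due to frailty. The Introduction already describes the comparator as matched on age, frailty and morbidity, while the Methods promise only best effort.

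**Working it through.** **1. The plan's own figure.** Sampling and sample size calculation states: "To detect a difference in chemotaxis with p<0.005 and 95% power, we will need to recruit eight CAP and eight controls". Its inputs are a 62% reduction and SDs of 0.079 (CAP) and 0.135 (controls). The control mean is not given, so the figure can only be solved backwards.
- Pooled SD = √[(0.079² + 0.135²)/2] = 0.1106.
- Normal formula, two-sided 0.005, 95% power, n = 8 per group: difference = 0.1106 × √(2/8) × (2.807 + 1.645) = 0.246, or 2.2 SD. The implied control mean is 0.246/0.62 = 0.40.
- Noncentral t: 2.6 SD, implied control mean about 0.47.

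The study therefore appears sized for an effect of about 2.2 to 2.6 SD. The protocol states no power for the matching check.

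**2. Continuous matching variables.** The two-sided 5% level is an assumption, because the protocol gives none for these comparisons. The noncentrality is d/√(1/n₁ + 1/n₂).
- 10 v 8: √(1/10 + 1/8) = 0.474, critical t (16 df) = 2.120. Any observed difference below 2.120 × 0.474 = 1.01 SD is non-significant.
- 8 v 8 (after the allowed drop-out): √(1/8 + 1/8) = 0.5, critical t (14 df) = 2.145, so the boundary is 1.07 SD.

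| True imbalance | t-test, 10 v 8 | t-test, 8 v 8 | Mann-Whitney, 10 v 8 (simulated) |
|---|---|---|---|
| 0.5 SD | 17% | 15% | 15% |
| 0.8 SD | 35% | 32% | 32% |
| 1.0 SD | 51% | 46% | 46% |
| 1.5 SD | 84% | 80% | not run |

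The t-test reaches 80% power only at 1.42 SD (10 v 8) or 1.51 SD (8 v 8).

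**3. Comorbidities.** Exact power of Fisher's test at 10 v 8 is 34% for 50% v 10%, 27% for 70% v 30% and 11% for 50% v 25%. An observed 6/10 v 1/8 gives p = 0.066, and 7/10 v 2/8 gives p = 0.15.

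**4. Effect on the CAP v control difference.** The shift in outcome SDs is the within-group correlation times the standardised imbalance. The protocol gives no correlation, so I assume 0.3 to 0.5. A 1 SD imbalance then shifts the unadjusted difference by 0.3 × 1 = 0.3 SD to 0.5 × 1 = 0.5 SD. Against the effect in step 1, that is between 0.3/2.6 = 12% and 0.5/2.2 = 23%.

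**5. Whether adjustment is feasible.** Simulating 8 v 8 with an assumed covariate-outcome correlation of 0.4, adjusting for age and frailty removed the bias. Power stayed above 90% at two-sided 5% for true effects of 2.2 to 2.6 SD.

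**The case against.** A reader might infer that matching rests entirely on tests run after recruitment, and that unmatched cohorts will therefore be reported as matched. The documents do not support that reading.
- Matching is planned at recruitment, on the clinical frailty scale and through the choice of clinics. Table 2 also excludes from both cohorts several conditions and treatments that affect neutrophils. The comparison is an additional check, not the only protection.
- Data collection names no test and calls the comparisons exploratory. A descriptive table would fit its wording, and using the tests in Statistical analysis is an inference.
- It gives no timing either. Recruitment is ongoing, so checking balance during it is compatible with the text.
- Nothing says that p > 0.05 will be taken to mean matched, and reporting is to follow the EQUATOR guidelines for observational studies.

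All of this stands, and it limits the point to the conditional form given here. It is also fair that the choice of balance statistic, or an adjusted analysis, may sit in a fuller document that is not shown. What remains is in the text itself: a comparison is given the task of ensuring balance, and the only between-group methods stated are poorly suited to judging it.

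One objection bears on the remedy. Standardised differences are noisy at this size. At 10 v 8, cohorts drawn from identical populations show an absolute difference above 0.25 about 60% of the time and above 0.5 about 31% of the time. They should be used to describe the cohorts and steer recruitment, not as a pass or fail rule.

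**Conclusion.** The point holds in limited form. The wording under Data collection asks a comparison to ensure something it can only describe. If the stated tests are used for it, they have about 17% to 51% power for imbalances of 0.5 to 1 SD at 10 v 8, so a non-significant result would be no evidence of balance. This rests on an assumed two-sided 5% level.

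The consequence for chemotaxis is moderate. Under the assumed correlations, a 1 SD imbalance moves the difference by 0.3 to 0.5 SD, which distorts the estimate. A reader might go further and suppose that confounding could account for the whole primary result. The figures do not support that, since the study appears sized for about 2.2 to 2.6 SD. The metabolic, oxidative-burst and surface-marker comparisons may be more exposed, but the protocol gives no effect sizes from which to judge. It is a worthwhile improvement because matching is best effort, the consent rules differ between cohorts and the stated comparison is unadjusted.

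**What to change.** - In Data collection, replace *ensure* with *describe*.
- For age, clinical frailty scale and the main comorbidities, report standardised differences (or differences in proportions) or individual values instead of p-values, and say that non-significance will not be read as matched.
- Review these figures while controls are still being recruited, so that the remaining controls can correct any drift.
- In Statistical analysis, add a sensitivity analysis of the chemotaxis comparison adjusted for age and clinical frailty scale, reported as an estimate with its confidence interval beside the unadjusted result.

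The cost is a few sentences and a small table, using data already being collected. The downside is lower precision from two extra covariates in 16 to 18 participants, confined to the sensitivity analysis. The chance to steer control recruitment ends when recruitment closes.

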**Figure 3 F3:**
[figure not shown]
Clinical data collected at study visits: at study visits, clinical information will be recorded in the following domains: demographic and social history, medical history, admission factors and outcome factors.

#### Blood sampling

For CAP participants, blood samples for research will be taken alongside clinically indicated blood samples to reduce number of venepuncture episodes for both CAP and control participants. Maximum of 45 mL blood will be taken at each study visit for research purposes.

#### Biological samples

Blood samples will predominantly be used in neutrophil isolation, processing and downstream use is described in table 3.

**Table 3 T3:** Biological sample processing

Vacutainer type	Volume (mL)	Purpose	Processing	Storage
Lithium Heparin	24	Neutrophil isolation	Described in text	N/A
Lithium Heparin	6	Plasma samples	Sedimentation at room temperature for 30 min followed by centrifugation at 560 rpm for 10 min.	500 µL aliquots at −80°C
EDTA	4	Plasma samples	As above	500 µL aliquots at −80°C
Plain	6	Serum sample	As above	500 µL aliquots at −80°C

N/A, not available.

#### Neutrophil isolation and functional assays

Isolated neutrophils will be prepared by discontinuous Percoll density centrifugation.^18^ Briefly, whole blood is gently mixed with 2% dextran in 6:1 ratio to enable sedimentation of red blood cells. Discontinuous Percoll solutions are prepared by diluting in either 1.54M NaCl or 0.154M NaCl to generate 90% and 56% solutions, respectively. The buffy coat is then layered over the discontinuous Percoll solution. The gradient is centrifuged at 470 g for 20 min at room temperature with no break or acceleration. The neutrophil layer is harvested and washed in phosphate buffered saline (PBS) to form a pellet. The neutrophils are resuspended in RPMI 1640 for downstream use. Neutrophils are typically >97% pure and >95% viable as assessed annexin/propidium iodide staining. Due to limitations in cell number, not all experimental assays will be carried out for each participant.

Neutrophil chemotaxis is assessed to a chemoattractant (interlukin-8) using a modified Insall chamber as described in.^26^ Use of the Insall chamber with time lapse filming using video microscopy allows for quantification of speed and directionality of individual neutrophils. To analyse the time lapse filming 10 neutrophils are selected at random and their movement tracked using FIJI Image J. These tracking data are then used to calculate speed, velocity, persistence and overall accuracy. Neutrophils migrate using proteinases to navigate extracellular matrices; therefore, speed and accuracy are important in assessing migratory parameters.^26^

Neutrophil lysates are prepared for RNA extraction and protein lysate for Western blotting and stored at −80°C. RNA will be used in RNA sequencing, targets identified involved in metabolism will be confirmed at the protein level.

Neutrophil oxidative burst is assessed using the Seahorse Analyzer (Agilent Technologies). In brief, neutrophils are treated with inhibitors of mitochondrial respiration (rotenone/anti-mycin A) followed by phorbol 12-myristate 13-acetate (PMA) treatment to generate RoS.^27^ Oxygen consumption is then measured to assess oxidative burst from the neutrophils over a time course. This method allows comparison of overall oxygen uptake and time taken to reach maximal oxygen uptake.

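### Tracking only 10 cells per film leaves avoidable sampling noise in the chemotaxis endpoint; tracking more is a cheap gain of unknown size, not a correction to n or power

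*Protocol article*

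**What the plan says.** The Abstract (Methods and analysis) names the endpoint: "The primary endpoint is neutrophil chemotaxis". The section on neutrophil isolation and functional assays describes how it is measured. The assay films cells in a chamber: "Use of the Insall chamber with time lapse filming using video microscopy allows for quantification of speed and directionality of individual neutrophils". The number of cells is then fixed: "To analyse the time lapse filming 10 neutrophils are selected at random and their movement tracked using FIJI Image J". The tracks feed several measures: "These tracking data are then used to calculate speed, velocity, persistence and overall accuracy".

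The section on sampling and sample size calculation builds the study on this endpoint: "Pilot data indicate a 62% reduction in chemotaxis in CAP cases with SD 0.079 for CAP and 0.135 for controls", and then "To detect a difference in chemotaxis with p<0.005 and 95% power, we will need to recruit eight CAP and eight controls". Recruitment allows for drop-out: "Total sample size: 10 CAP and 8 controls".

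The article gives no reason for 10 cells. It reports no within-participant or between-participant variance, and it does not mention replicate films. The functional assays section does say that cell numbers are limited, but that remark concerns which assays a participant's sample can support. It does not concern how many filmed cells can be tracked.

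**The concern.** A participant's value has two sources of variation that matter here. One is how participants differ from each other. The other is the error from judging a participant by a handful of cells. Only more participants can offset the first. More tracked cells reduce the second.

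Participants are the scarce resource: 18 are planned, over a recruitment period given as March 2020 to November 2024. Tracks from a film that already exists are much cheaper. Fixing the cell count at 10 with no stated reason therefore limits precision at the least costly step of the chain.

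At stake is the width of the interval for the CAP versus control difference, and the reserve of power if the true effect is smaller than the pilot suggested. Within-person change across the CAP visits is also affected. There, stable differences between people cancel, while cell-sampling error enters at both visits.

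**Working it through.** **Inputs from the protocol article.** Cells per film: 10 (functional assays section). From the sample size section: "SD 0.079 for CAP and 0.135 for controls", a 62% relative reduction, p<0.005, 95% power, 8 v 8. Test: independent-sample t-test or a non-parametric equivalent (Statistical analysis).

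**Step 1: the plan's own figure.** The stated 8 per group can be neither confirmed nor refuted, because no control mean is given and a 62% reduction cannot be turned into an absolute difference. Working backwards:
- Root-mean-square SD = √[(0.079² + 0.135²)/2] = 0.1106.
- With two-sided alpha 0.005 (sidedness is not stated) and the noncentral t distribution, 8 per group is the smallest number reaching 95% power if the difference lies between about 0.288 and 0.318. Dividing by 0.62 gives a control mean of about 0.47 to 0.51.
- So 8 is plausible but unverified. The difference 0.288, which gives exactly 95.0% power at 8 v 8, is used below as the design effect.

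**Step 2: effect of the number of cells.** For a participant value that is the mean of m independently sampled cells,

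Var = σ²(between) + σ²(cell)/m.

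Let f be the share of the variance at m = 10 that comes from cell sampling. Relative to 10 cells, the variance ratio is 1 − f + f × 10/m. At m = 30 this is 1 − 2f/3.

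The document does not give f, so a range is assumed. It is also assumed that the pilot SDs came from 10 cells. The last two columns are power at 8 v 8 with 30 cells.

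| f (assumed) | Variance ratio | SD ratio | SD cut | Equivalent n per group, 8/ratio | Power at design effect (95.0% with 10 cells) | Power at 75% of that effect (70.9% with 10 cells) |
|---|---|---|---|---|---|---|
| 5% | 0.967 | 0.983 | 2% | 8.3 | 95.7% | 72.8% |
| 10% | 0.933 | 0.966 | 3% | 8.6 | 96.4% | 74.7% |
| 25% | 0.833 | 0.913 | 9% | 9.6 | 98.0% | 80.6% |
| 50% | 0.667 | 0.816 | 18% | 12.0 | 99.6% | 90.1% |

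**Step 3: what these shares imply.** With 10 cells, the intraclass correlation between cells of one participant is (1 − f)/(1 + 9f). For f = 5%, 10%, 25% and 50% this is 0.66, 0.47, 0.23 and 0.09. The larger gains therefore need cells from one participant to resemble each other only weakly. At an intraclass correlation of 0.5 or 0.7, 30 cells would cut the SD by only 3% or 1.4%.

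**Step 4: workload.** If there is one film per visit, there are at most 10 × 3 + 8 = 38 films, each with about 20 additional tracks.

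**The case against.** The strongest reply is that nothing is shown to be wrong. A reader might infer from the 10-cell rule that the study is underpowered or that n is miscalculated. The document does not support that: if the pilot used the same 10-cell assay, its SDs already include the cell-sampling noise, and so does the stated power. The article does not say how many cells the pilot used. This part of the reply stands.

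It is also true that the size of the gain rests wholly on an assumed f. Equivalents such as 9.6 or 12 participants per group should not be read as estimates. If differences between participants dominate, the gain is a few per cent or less.

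Several practical premises are unstated as well. Random selection implies more than 10 visible cells, but it does not show that 30 are trackable. The article does not say that films are kept, that there is one film per visit, or that tracks are averaged to one value per participant. The reason for 10 may lie in the cited method or the full protocol. A rule of 30, or all cells if fewer, could also let the count vary between participants and perhaps between groups.

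These points reduce the claim but do not remove it. Averaging more randomly chosen cells cannot worsen the precision of a participant's mean. Comparability can be protected by one rule for every film and a parallel 10-cell result.

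**Conclusion.** The point holds as an inexpensive improvement. The 10-cell rule leaves avoidable cell-sampling noise in the primary endpoint of an 8 v 8 comparison. Moving to 30 cells would cut the participant-level SD by about 2% to 18% for assumed shares f of 5% to 50%, so the benefit could be small.

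This rests on four assumptions: the pilot SDs came from 10 cells, there is one film per visit, tracks are averaged within participant, and enough further cells can be tracked. It is not a finding of inadequate power or of an error in the sample size. It concerns precision only, not how cells are chosen.

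**What to change.** In the section on neutrophil isolation and functional assays, replace the count of 10 with a larger fixed target of randomly selected cells per film, for example 30, or all trackable cells if fewer. The figure of 30 is illustrative; if the pilot's within- and between-participant variances are available, use them to set the target or to justify keeping 10.

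State also that:
- the tracks are reduced to one mean per participant and visit, so that cells do not add to n;
- the same rule applies to CAP participants and controls, and to all retained films;
- the number of cells tracked per film is reported by group;
- the 10-cell value is reported as a sensitivity analysis.

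The cost is operator time: about 20 extra tracks on each of at most 38 films, and more if replicate films exist. No further blood, consent or participants are needed. Earlier films can be re-tracked only if they were kept. If they were not, those participants remain at 10 cells and the report should say so.
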